Since the first detection of the XBB Omicron subvariant in August 2022 in India, it has been detected in more than 17 countries to-date including Singapore, Australia, Bangladesh, Denmark, Japan and the US. The current wave of COVID-19 cases in Singapore, driven by the XBB strain, is expected to peak in mid-November 2022 with about 15,000 daily cases on average. The proportion of reinfections among total COVID-19 cases in Singapore is also on the rise, currently making up about 17% of total new cases. To combat the rising COVID-19 infections and reinfections, the bivalent Moderna/Spikevax vaccine was added to the National Vaccination Programme from 14 October 2022 for persons who have yet to achieve minimum protection (i.e. received at least 3 doses of mRNA/Nuvaxovid or 4 doses of Sinovac-Coronavac), or those aged 50 years and above who have received their last vaccine dose more than five months ago. On 25 October 2022, Singapore's HSA granted interim authorisation of a booster dose of the Pfizer-BioNTech bivalent vaccine for individuals aged 12 years and older.

From 14 Nov 2022, a second booster dose from five months to one year after the last vaccine dose is recommended by MOH for all individuals aged 18 years or older.

The updated bivalent vaccine is preferred for this. A person is considered up-to-date with their COVID-19 vaccination if they have received at least the minimum protection and their last vaccine dose was received within the past one year. The bivalent Moderna/Spikevax vaccine is currently available, and the bivalent Pfizer-BioNTech vaccine is expected to be available by the end of this year.

PRIBIVAC will assess a heterologous prime-boost-boost strategy in comparison with a homologous regimen in order to compare short and long-term immunogenicity of different COVID-19 vaccine combinations against the ancestral SARS-CoV-2 as well as different VOCs. Initial phases of the study have studied homologous versus heterologous vaccines at the first booster, later phases will study these as the second booster.

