| Exploratory objectives                                                                                                                                                                                                                                                                                                                                                                                  |                                                                                                                                                                                                                                                                                                                     |                         |
| 
To determine whether vaccine efficacy differs between heterologous and homologous prime-boost-boost regimens
                                                                                                                                                                                                                                                                                            | 
PCR-confirmed COVID-19 infections as recognised by Ministry of Health, Singapore
 
Positive for COVID-19 on self-administered Antigen Rapid Test (ART)/supervised self-administered ART/medical professional administered ART, in accordance with the Ministry of Health recommendations and guidelines
 | Throughout the study    |
| 
To characterise and compare the mucosal immune response in nasal swab and saliva following COVID-19 vaccination with heterologous and homologous prime-boost-boost regimens
                                                                                                                                                                                                                             | Level of SARS-CoV-2 anti-spike immunoglobulins                                                                                                                                                                                                                                                                      | Day 1, 7, 28, 180, 360  |

|                                                                                                                                                                    |                                                                                       |       |

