### **3.4. Exclusion Criteria**

1. Known history of SARS-CoV-2 or SARS-CoV-1 infection;
2. Previously received an investigational coronavirus vaccine;
3. Previously received a SARS-CoV-2 monoclonal antibody;
4. Current or planned simultaneous participation in another interventional study;
5. A history of anaphylaxis, urticaria, or other significant adverse reaction requiring medical intervention after receipt of a COVID-19 vaccine, or otherwise have a contraindication to one of the available study vaccines per the approved label;
6. Individuals who are immunocompromised (e.g. active leukaemia or lymphoma, generalised malignancy, aplastic anaemia, solid organ transplant, bone marrow transplant, current radiation therapy congenital immunodeficiency, HIV/AIDS with CD4 lymphocyte count  $< 200$  and patients on immunosuppressant medications);
7. Received systemic immunosuppressants or immune-modifying drugs for  $>14$  days in total within 6 months prior to Screening (for corticosteroids  $\geq 20$  milligram per day of prednisone equivalent). Topical tacrolimus is allowed if not used within 14 days prior to Day 1;
8. Individuals who are pregnant or breast feeding;
9. Chronic illness that, in the opinion of the study team, is at a stage where it might interfere with trial conduct or completion;
10. Deprived of freedom by an administrative or court order, or in an emergency setting, or hospitalised involuntarily;
11. Current alcohol abuse or drug addiction that might interfere with the ability to comply with trial procedures in the opinion of the study team;
12. Moderate or severe acute illness/infection (according to study team's judgement) on the day of vaccination, or febrile illness (temperature  $\geq 37.5^{\circ}\text{C}$ ). A prospective participant should not be included in the study until the condition has resolved or the febrile event has subsided.

For Phase D of the trial exclusion criteria 1 and 4 will no longer apply: exclusion criteria 1 is no longer relevant as it not a consideration in MOH recommendations for COVID-19 booster vaccination, and exclusion criteria 4 because of the broad recommendations from MOH for keeping up to date with COVID-19 boosters.

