**Footnotes:**

 Screening visit may be performed on the same day as Visit 1

 Informed consent must be signed prior to initiating any study procedures;

 Randomisation is subjected to vaccine availability;

 Visit 1: third vaccine shot for participant (first and only vaccine administered for the study);

 Physical examination will be done by a qualified study team member or a treating licensed healthcare provider. The physical examination on visit 1 will be conducted during screening prior to vaccination;

 Vital signs include pulse, systolic and diastolic blood pressure, respiratory rate and body temperature prior to vaccination and blood collection;

 For women of child bearing potential a urine pregnancy test will be conducted for Phases A-C of the study, and not for Phase D;

 At each study visit, a review for PCR-confirmed COVID-19 infection will be conducted. In most cases, such information will be available in the participant's HealthHub app. In addition, a review for any positive COVID-19 detected by self-administered Antigen Rapid Test (ART)/supervised self-administered ART/medical professional administered ART will be conducted. For positive results, the category of ART (whether it was self-administered or supervised or administered by a medical professional), the brand of the ART kit used (only if self-administered), and the date of ART positive will be captured;

 All AEs including a list of solicited and other events will be recorded for 7 days after vaccination (see diary version 3.0). Unsolicited AEs will be recorded up to day 28 after vaccination. SAE will be recorded from first vaccination until the end of study period at 12 months. They will be assessed via the listed study procedures, safety laboratory tests, and participant self-recorded diary;

 Safety laboratory bloods will only be monitored during Phases A-C of the study, and not for Phase D

 Haematology tests include full blood count with differential and platelet counts;

 Liver panel includes Albumin, total bilirubin, alkaline phosphatase (ALP), alanine transaminase (ALT); Renal panel includes sodium, potassium and creatinine;

 Cardiology panel include creatine kinase, troponin;

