### **8.6. Concomitant therapy**

There will be no restrictions on diet, exercise or concomitant medication imposed on participants, except for the restriction of receiving any other COVID-19 vaccines outside of this study.

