## **11.2. Statistical and Analytical Plans**

### *a. General Considerations*

The safety analysis set consists of all participants who received the study vaccine. The efficacy analysis set is defined as all participants who are assessable with respect to immunogenicity after receiving the study vaccine. The analysis will include all study arms, including those in which participant enrolment is discontinued following interim analysis. Separate set of analyses will be done for Phase A-C and Phase D.

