### *c. Efficacy Analyses*

Graphical plots will be produced for the various immunity endpoints to depict the change of immunity levels over time. Levels of SARS-CoV-2 anti-spike immunoglobulins will be summarized by study arm and by randomisation stratification factors. Mean difference and its 95% CI in levels of SARS-CoV-2 anti-spike immunoglobulins between an intervention arm and the control arm (for Phase A-C), and between pairwise arms (for Phase D) will be estimated from a general linear regression model which adjusts for level of SARS-CoV-2 anti-spike immunoglobulins at baseline, and randomisation stratification factors. If the lower bound of the 95% CI of Phase A-C SARS-CoV-2 anti-spike immunoglobulins falls above -10% (the pre-specified non-inferiority margin), non-inferiority of the intervention arm will be concluded. For Phase D, reported mean differences and 95% CIs are exploratory in nature. Analysis of repeated measurements of immunity endpoints will be performed with the use of mixed effects models that adjust for baseline values and randomisation stratification factors. Log-transformation of the data may be applied as needed before the analyses.

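### Day 180 and Day 360 immunity comparisons, as written, combine response to the study vaccine with response to later SARS-CoV-2 infection, and no analysis separates the two

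*Protocol*

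**What the plan says.** Protocol 11.2 a fixes who is analysed: "The efficacy analysis set is defined as all participants who are assessable with respect to immunogenicity after receiving the study vaccine". Protocol 11.2 c fixes how the longitudinal data are handled: "Analysis of repeated measurements of immunity endpoints will be performed with the use of mixed effects models that adjust for baseline values". The strata used at randomisation are adjusted for too. No other covariate and no rule about samples is named.

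The late time points are formal objectives. The table in 2.2 lists anti-spike, neutralising antibody and T-cell measures at Days 180 and 360 as secondary outcomes. For Phases A-C that secondary objective is worded as non-inferiority.

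Infections are recorded. Footnote 8 to the schedule in section 4 says: "At each study visit, a review for PCR-confirmed COVID-19 infection will be conducted". It adds positive antigen rapid tests (ART), with their date. Two uses are stated: an exploratory vaccine-efficacy outcome in 2.2, which counts "PCR-confirmed COVID-19 infections as recognised by Ministry of Health, Singapore" and positive ARTs, and safety monitoring by the principal investigator in Phase D (9.4). Neither is linked to the immunity models.

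Infection before entry is handled differently by phase. Phases A-C exclude a known history of infection. For Phase D, 3.4 says: "For Phase D of the trial exclusion criteria 1 and 4 will no longer apply", and criterion 1 is the infection exclusion.

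On other vaccine doses, 8.6 leaves concomitant treatment free "except for the restriction of receiving any other COVID-19 vaccines outside of this study". It gives no analysis consequence for a breach.

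**The concern.** A breakthrough infection raises the same anti-spike, neutralising and T-cell measures that the trial uses to compare vaccines. Adjusting for baseline deals with infection before the study dose, not after it. A Day 180 or Day 360 value drawn after an infection therefore enters the model as if the study vaccine had produced it.

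Exposure is not remote. Phase A recruitment opened on 12 October 2021 (1.2 d) and follow-up lasts a year, so it runs through the Omicron period. Section 1.2 a describes an XBB wave expected to average about 15,000 cases a day at its peak. The same section names background infection rates as a possible confounder when it discusses the relevance of other countries' data to Singapore.

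At stake is the long-term immunogenicity conclusion. If the less protective vaccine has more infections, its late titres rise for that reason. In Phases A-C, a difference that shrinks in this way makes it easier to conclude late non-inferiority.

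**Working it through.** **1. Reproduce the plan's precision figure (11.1, Phase D).** Inputs: SD 0.32 log10, 50 per arm, 5% dropout, half-width 0.13.

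- Half-width = 1.96 × SD × √(2/n).
- Required n = 2 × (1.96 × 0.32 / 0.13)² = 46.6, so 47 evaluable per arm. 46.6 / 0.95 = 49.0, in line with the stated 50.
- At n = 47: 1.96 × 0.32 × √(2/47) = 0.129. The stated 0.13 is reproduced. It is a Day 28 planning figure, and nothing in this point shows it to be wrong.

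**2. What infection can do to a late comparison.** The protocol gives no infection rate per participant and no size for the rise after infection, so everything in this step is assumed. Let the vaccine-only gap be 0.20 log10, the infected fractions pS (stronger arm) and pW (weaker arm), and the rise b.

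- Additive pattern (each infected person gains b): observed gap = 0.20 + b(pS − pW).
- Plateau pattern (each infected person reaches a common level b above the stronger arm's uninfected mean): observed gap = b(pS − pW) + 0.20(1 − pW).

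| Pattern | b | pS / pW | Observed gap |
|---|---|---|---|
| Additive | any | equal | 0.20 |
| Plateau | any | 20% / 20% | 0.16 |
| Plateau | any | 40% / 40% | 0.12 |
| Additive | 0.5 | 20% / 40% | 0.10 |
| Plateau | 0.5 | 20% / 40% | 0.02 |
| Plateau | 0.8 | 20% / 40% | −0.04 |
| Plateau | 0.5 | 40% / 30% | 0.19 |
| Additive | 0.5 | 40% / 30% | 0.25 |
| Additive | 0.8 | 40% / 30% | 0.28 |

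For example, the fifth row is 0.5 × (0.20 − 0.40) + 0.20 × 0.60 = −0.10 + 0.12 = 0.02. The gap can be unchanged, attenuated, reversed or widened.

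**3. Precision cost of setting infected samples aside.** Start from 47 evaluable per arm and assume that SD 0.32 still holds at the late visits.

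- 20% infected: n = 37.6, half-width 1.96 × 0.32 × √(2/37.6) = 0.145.
- 40% infected: n = 28.2, half-width 1.96 × 0.32 × √(2/28.2) = 0.167.

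The relative widening is 1/√(1 − p), that is 1.12 and 1.29, whatever the starting number per arm.

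**4. Keeping the samples also costs precision.** Under an assumed 30% infected and an additive rise of 0.7, the mixture SD is √(0.32² + 0.3 × 0.7 × 0.7²) = 0.453, or 1.41 times 0.32.

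**The case against.** **The protocol never says that post-infection samples are kept, and an unseen SAP may deal with them.** This is fair as far as it goes: retention is inferred from the all-assessable set and the absence of any rule. But the protocol does fix the set and the covariates. Following them through the Omicron and XBB waves gives the mixed comparison, so this is more than a detail left open.

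**Direction.** A reader might infer that the plan necessarily pulls the arms together and biases towards non-inferiority. The documents do not support that. It requires a plateau, or more infection in the weaker arm. Nothing in the protocol shows that the heterologous mRNA arm protects less.

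**Scale.** The −10% margin was set on surrogate neutralisation percentages (mean 84%, SD 15%, in 11.1). The log10 illustrations do not convert to that scale, so the effect on a non-inferiority conclusion is not quantified.

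**Extra vaccine doses.** Section 1.2 a says that, from 14 November 2022, "a second booster dose from five months to one year after the last vaccine dose is recommended by MOH" for all adults. A reader might infer widespread extra doses before Day 360. Section 8.6 bars them. In Phase D the study dose is itself the second booster. A Phase A-C participant vaccinated by mid-March 2022 reached Day 180 in September 2022, before that advice. Earlier second-booster programmes (selected people from March 2022, ages 50 and over from October 2022) leave some room for breaches. However, the schedule has no item that records non-study doses, so this is a minor limb.

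**Setting samples aside is not neutral.** This stands. If people with low titres are infected more often, those left uninfected in the weaker arm are selected for high titres, and some attenuation remains. Whether to include or set aside post-infection values is a choice of estimand, and neither choice is an error in itself. That is why the second analysis belongs beside the all-data model and should not replace it.

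**Conclusion.** The point holds for the secondary Day 180 and Day 360 comparisons. As written, they estimate vaccine response plus whatever later infection adds, and no planned analysis separates the two, although the infection data are collected. Under the stated assumptions a true gap of 0.20 log10 could appear as anything from −0.04 to 0.28. Those values show that direction and size are open; they do not predict the trial's result. Where attenuation occurs, it favours a late non-inferiority reading in Phases A-C.

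A reader might extend this to the primary result. The documents do not support that: the primary time point is Day 28 (±7 days), which leaves little time for infection to intervene. Phase D tests no hypothesis and calls its estimates exploratory, so there the issue is interpretation and not a false claim. No figure in the sample-size section is wrong on this account.

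**What to change.** In Protocol 11.2 c, for Days 180 and 360:

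- Add a pre-specified analysis of the immunity endpoints that sets aside each participant's samples from the first recorded positive PCR or ART onward. Apply the same rule after a non-study COVID-19 vaccine dose, or where anti-N results show infection in recipients of spike-only vaccines, if such data exist. The assay description in 6.3 lists N peptides only as one of several options, so anti-N is not assured.
- Report this analysis beside the all-data model, with the number infected per arm by each visit.
- Conclude late non-inferiority in Phases A-C only if both analyses support it. Enrolment to those phases is over, so the addition should be dated and made before the late comparisons are examined.

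The cost is mainly wording. The review at each visit at least places an infection between two visits, which is enough to apply the rule. The price is fewer late samples: the 0.13 half-width becomes about 0.145 if 20% are infected and 0.167 if 40% are, at SD 0.32. Censoring may also be informative, and the all-data model does not fully resolve that; the report should say so.

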### *d. Describe the types of statistical interim analyses and stopping guidelines (if any) that are proposed, including their timing.*

For Phase A-C of PRIBIVAC interim analyses will be performed for DSMB review after 10 participants from each of the intervention arm have completed assessments at study day 28.

DSMB may recommend discontinuation of participant enrolment to a study arm if any of the following criteria is met:

- Proportion of participants with SAE is at least 25% greater (in absolute difference) in the intervention arm compared with the control arm
- Proportion of participants with Grade 3 and 4 AEs is at least 25% greater (in absolute difference) in the intervention arm compared with the control arm
- Geometric mean ratio of anti-SARS-CoV-2 between the intervention arm and the control arm falls below 0.60.

The above guidelines may be revised in the DSMB charter, which implies the stopping guidelines will take precedence should there be any difference in the guidelines between the protocol and the DSMB charter.

For phase D of the study no formal stopping guidelines are provided, and no further data and safety review by DSMB will occur.

## **12. ETHICAL CONSIDERATIONS**

### **12.1. Informed Consent**

The PI is responsible for ensuring regulatory approval is obtained for the study.

The PI is also responsible for obtaining Institutional Review Board (IRB) approval for the protocol, and ensuring participant information sheet and ICF are in compliance with local regulatory requirements prior to enrolling any participant into the study. The approval letter/document must clearly identify the protocol and all documents approved by the IRB, including version number, date of the protocol, participant information sheet and ICF. The PI must also obtain approval for any amendments to the protocol or participant information sheet and ICF. The PI must comply with all IRB reporting requirements for all AEs, annual updates, end of study reports, and must agree to abide by any IRB conditions of approval. The PI (or designee) is responsible for ensuring freely-given consent is obtained from each potential participant prior to the conduct of any protocol-specific procedures. The PI may delegate the task of obtaining consent to appropriately qualified co-investigator(s). Consent must be documented by the participant's dated signature on the participant information sheet and ICF together with the dated signature of the person conducting the consent discussion.

If the participant is illiterate or a translator is required, an impartial witness should be present during the entire consent discussion. Once the discussion is complete, the participant must sign and date the ICF, if capable. The impartial witness must also sign and date the ICF along with the person who conducted the consent discussion.

A copy of the signed and dated participant information sheet and ICF must be given to the person prior to study participation. The participant must be informed in a timely manner of any new information that becomes available during the course of the study that may affect his/her willingness to continue study participation.

This study shall be conducted in accordance with the ethical principles laid out in the Declaration of Helsinki (most current issued version) and the National Statement on Ethical Conduct in Research Involving Humans (most current issued version).

## **12.2. IRB review**

All relevant documents will be approved by the NHG DSRB before trial initiation in Singapore.

## **12.3. Confidentiality of Data and Patient Records**

All study findings and documents will be regarded as confidential. The investigators and other study personnel must not disclose such information without prior written approval from the PI. Participant confidentiality will be strictly maintained to the extent possible under the law and local hospital policy. Identifiable information will be removed from any published data.

